### Blinding

Participants and intervention delivery facilitators cannot be blinded to group allocation. Evaluators conducting the clinical, neurophysiological (EEG and EMG), and physical (kinematics) assessments will be blinded to group allocation.

### Interventions

#### Overview

For all groups of participants (ie, EG@Hosp, EG@Home, and CG), the intervention will include 15 sessions spanning 5 weeks (3 sessions per week) in addition to the conventional motor rehabilitation program expected for each patient’s condition. Motor rehabilitation will be based on the relevant ADL that include at least one of the following: feeding, self-care, or external actions on the affected side. A total of 5 different videos (with the same motor task) will be presented in each session, beginning with the easiest action and ending with the most complex action. Each session will last approximately 15 minutes and will be repeated twice a day, at least 60 minutes apart.

#### AOT Protocol for EG@Hosp

Participants will be asked to carefully observe the videos showing different daily actions. Each motor act will be presented for 2 minutes. At the end of each motor act presentation, participants will execute the observed motor sequence for 1 minute (without any verbal instructions) with the affected upper limb.

Participants enrolled in EG@Hosp will perform rehabilitation treatment in the hospitals’ premises.

The video will be played on a 15-inch monitor at a distance from the participant such that there will be sufficient space to perform the required movements. During the repetition of the motor action, a black screen will appear on the monitor.

#### AOT Protocol for EG@Home

After appropriate training of patients and caregivers, the use of tablets will allow home-based treatment. In particular, a tablet will be enabled with a web-based program that will be used to train the patients (and receive feedback on their progress).

Participants enrolled in EG@Home will be asked to carefully observe the videos showing different daily actions on the tablet. The web-based program will present each motor act for 2 minutes. At the end of each motor act presentation, the web-based program will ask the participants to execute the observed motor sequence for 1 minute (by audio or video message) with the affected upper limb.

Participants enrolled in EG@Home will perform rehabilitation treatment at their homes.

A 7-inch tablet with Android software 11.0 will be used for the experimentation. Before handing the tablet to the patient, the researcher will schedule the AOT program via the web, defining the days when the patients should perform the treatment independently at home. Patients can check the days on which treatment will be performed by consulting the web-based application, specifically the section where the scheduling of sessions is provided, on the tablet. The research teams will be remotely monitoring the progress of the EG@Home sessions using a dedicated web platform.

The web-based application was developed by a specialist following the researchers’ specification.

#### CG Protocol

The participants will be asked to observe video clips with no content on human motor activities. Videos will concern scientific, geographical, and historical issues.

For EG@Hosp and EG@Home, 5 different video clips (each 2 minute long) will be presented during each session. At the end of each video, and after the therapist’s verbal instructions, participants will execute the motor task actions for 1 minute with the affected upper limb.

In this way, both the groups and controls will undergo the same amount of motor practice and receive the same amount of visual stimulation, with the only difference being the visual stimulus content.

Participants enrolled in the CG will perform rehabilitation treatment in the hospitals’ premises.

The video will be played on a 15-inch monitor at a distance from the participant such that there will be sufficient space to perform the required movements. During the repetition of the motor action, a black screen will appear on the monitor.

### Assessment: Instrumental Setup

The assessment setup and protocol will be the same as those used in similar studies [33,41] for the evaluation of impaired upper extremity functionality. The participant will sit in front of a target panel (eg, a 24-inch touch screen monitor) to perform the pointing task evaluation test.

The panel will have 9 targets; 8 of these, arranged in a circle, will be positioned 20 cm from its center, that is, the ninth target. The center of the target panel will be aligned with the shoulder acromion of the impaired upper limb. The distance between the participant and the center of the panel will be set according to each participant’s arm length measured with the fist closed. During the pointing task trials, the participants will be instructed to reach, at their self-selected speed, one of the 9 targets on the board.

All the participants enrolled in this study will perform assessment tasks in the hospitals’ premises.

### Assessment: Primary and Secondary End Points

#### Overview

A thorough assessment of the clinical improvement in the functionality of the affected upper extremity will be performed using the FMA-UE (primary outcome), which will be combined with other clinical scales (secondary clinical outcomes).

In addition, the secondary instrumental outcomes (ie, EEG, EMG, and kinematics) will be included to verify neural plasticity and motor recovery using neurophysiological and kinematic parameters.

In addition, only for home-based treatment (EG@Home) group, the usability of the platform and the participants’ satisfaction with the services will be evaluated using a specific questionnaire (Technology Acceptance Model [TAM]) and a nonstructured interview.

The variables related to the secondary instrumental outcomes (ie, EEG, EMG, and kinematics) will be evaluated during the standardized pointing task described earlier.

All the data will be analyzed using MATLAB software (MathWorks Inc). Specifically, the EEG recordings will be preprocessed offline using the MATLAB’s toolbox called *EEGLAB* for artifact removal.

#### The Functionality of the Affected Upper Extremity

To perform a thorough assessment, different motor components of the affected upper extremity will be evaluated using the FMA-UE combined with 6 other scales.

The FMA-UE [34,35] (primary outcome) is a stroke-specific, performance-based impairment index. It is designed to assess motor function, balance, sensation, and joint function in patients with poststroke hemiplegia.The Frenchay Arm Test [36] is a measure of upper extremity proximal motor control and dexterity during ADL performance in patients with impairments resulting from neurological conditions. The Frenchay arm test is an upper extremity–specific measure of activity limitation.The Box and Block Test [42] assesses the unilateral gross dexterity of the hand. It requires participants to move as many blocks as possible from one side to the other in 1 minute.The Modified Ashworth Scale [43] measures resistance during passive soft tissue stretching and is used as a simple measure of spasticity of all movements of the different joints of the upper extremity.The Modified Barthel Index [44] is an ordinal scale used to measure ADL performance. Each performance item is rated on this scale, with a given number of points assigned to each level or ranking. It uses 10 variables to describe ADL and mobility.The Motor Activity Log [45] assesses the quantity (*amount* subscale) and quality (*how well* subscale) of the use of the upper limb during ADL performance.The Nine Hole Peg Test [46] measures hand dexterity. This requires participants to repeatedly place and then remove 9 pegs into 9 holes, one at a time, as quickly as possible.

#### Neurophysiological Biomarkers

The following biomarkers will be used in the study:

The EEG signal will be recorded (0.01-100 Hz band pass; sampling frequency: 1024 Hz) using 64 to 128 electrodes (high-density EEG, system 10-10 increased) during the pointing task (described earlier). Alpha (8-13 Hz), beta (14-30 Hz), and mu (8-13 Hz) bandwidths will be registered. EEG biomarkers will be ERD and ERS of alpha and beta rhythms, beta brain coherence, and mu rhythm suppression [47-50].Surface EMG signals from the activation of 2 pairs of agonist and antagonist muscles from 4 upper arm and shoulder muscles (brachial biceps, brachial triceps, anterior deltoid, and posterior deltoid) will be recorded. Dual Ag-AgCl snap electrodes with an interelectrode spacing of 2 cm will be used during the acquisitions. A standard procedure, in accordance with Surface ElectroMyoGraphy for the Noninvasive Assessment of Muscles recommendations [51], will be used for skin preparation and electrode placement. The reference electrode will be placed over the electrically neutral lateral wrist epicondyle. The outcome of this analysis will be the cocontraction index calculated during the initial portion (epoch) of the single pointing movement (forward and return movement will be analyzed separately), which is identified as the acceleration phase of the hand kinematics.

#### Kinematics

Kinematic parameters of the pointing motor task will be acquired at 100 Hz by using a 7-camera motion capture system (Vicon, Oxford Metrics Ltd). Spherical reflective markers for motion tracking will be placed on specific body landmarks. In addition, an inertial measurement unit will be placed over the metacarpophalangeal joint of the middle finger.

The data acquired during the assessment trial with respect to the hand trajectory (ie, metacarpophalangeal joint of the middle finger) will be evaluated using the following metrics, related to the entire turn [52]:

Number of peaks of the speed profile: If a point-to-point reaching movement has a low number of peaks, it means that few acceleration and deceleration periods are present [53].The smoothness described by Teulings’s index is the rate of change of the acceleration in a movement [54]; a lower value of Teulings’s index indicates a smoother movement.Movement accuracy will be evaluated using the normalized path length parameter, as described by Colombo et al [55]; essentially, it is the line obtained by normalizing the effective length path with the ideal path; when this parameter approximates 1, the movement accuracy is very high.The absolute hand path error, as computed by Franklin et al [56], is the area between the actual movement path and the straight line; this is considered an index of learning, and a reduction of this metric indicates a better adaptation to the required task.

#### Usability of the Platform (Only for Home-Based Treatment)

The feasibility of the home-based treatment and the usability of the platform, as well as the participants’ satisfaction with the services, will be assessed by patients at the end of the intervention (T2) with the following scales:

TAM [57] includes 3 criteria (perceived ease of use, perceived usefulness, and behavioral intention to use). A Likert scale has been developed in which the user will rate from 1 to 7 whether they agree with a series of statements.Nonstructured interviews (adapted from the TAM) to investigate patients’ feelings.

### Sample Size

As the changes in the effects of upper limb AOT in patients with stroke on EEG biomarkers have not been previously investigated, we have estimated the sample size based on previously published studies [58,59], comparing AOT and conventional therapy. We estimated the sample size required to detect differences in the effects of “group”×“time” interactions on primary clinical outcome (FMA-UE).

For this outcome, an effect size of 0.495 [60,61] is expected based on previous studies. Given the expected effect size, a total sample size of 54 will be required for repeated ANOVA with a power of 0.8 and a 2-sided type-I error of 0.05 (number of groups=3 [ie, EG@Hosp, EG@Home, and CG]; number of measurements=3 [ie, T1, T2, and T3]). Therefore, when considering a dropout rate of 10%, we plan to recruit 20 participants for each group (a total of 60 participants) for this study.

### Statistical Analysis

#### Baseline Comparability Analysis

The baseline characteristics of the participants will be summarized and compared. These include the descriptions of demographic data, symptoms, and general conditions. The 2-tailed *t* test or nonparametric statistical method will be used for quantitative data. Categorical data will be analyzed using chi-square or Fisher exact tests and the Wilcoxon test.

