## Methods

### Overview

A randomized, parallel-arm, controlled, outcome measurer–blinded, and multicenter clinical trial conducted in 2 neurorehabilitation centers in Italy aims to investigate the effectiveness of AOT in patients with chronic stroke (ie, >6 months from the first event) using quantitative EEG biomarkers, confirming the translational power of a tailored treatment.

A total of 60 individuals who have been enrolled will be randomized to the experimental group in hospital (EG@Hosp), experimental group at home (EG@Home), or control group (CG) in a 1:1:1 ratio.

The EG@Hosp will observe and execute ADL that are task-oriented actions (AOT protocol); the EG@Home will observe and perform the same ADL at home (AOT protocol at home); and the CG will not observe any motor task videos (but will watch video only on landscapes and historical issues), and after verbal instructions, they will perform the same actions observed by the other 2 groups.

After completing the patient screening, randomization will be performed before the first treatment session (T0). At baseline (T0), midintervention (after the 7th session; T1), and after the intervention (15th session or 5th week; T2), outcomes (ie, clinical scales, EEG and electromyography [EMG] signals, and kinematic parameters) will be assessed to evaluate impairment and functional abilities.

For each group, the total duration of the intervention will be 5 weeks (3 times a week) for a total of 15 sessions. After the end of the intervention, a 2-month follow-up assessment period (T3) will be scheduled to assess the maintenance and long-term effects.

The primary outcome assessed at T2 will be assessed by the Fugl-Meyer Assessment-Upper Extremity (FMA-UE) scores.

The trials will be performed at 2 neurorehabilitation centers in Italy: IRCCS San Raffaele Roma Hospital in Rome and at Casa di Cura del Policlinico Hospital in Milan.

All the data will be recorded in electronic case report forms through the REDCap (Research Electronic Data Capture; Vanderbilt University) system, accessed on the web via the internet for data collection and management.

A specific route diagram is presented in Figure 1. The protocol for this study was developed in accordance with the Standard Protocol Items: Interventional Trial Recommendations guidelines (SPIRIT) [40].

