#### Analysis of the Effectiveness

Analysis of the primary outcome (ie, functionality of the affected upper extremity) will be performed using the per-protocol principle. Treatment effects will be compared using a 2-way repeated ANOVA for clinical measurements, considering “time” (3 levels: T0, T1, and T2) as a within-subject factor and “group” (3 levels: EG@Hosp, EG@Home, and CG) as a between-subject factor.

In addition, the percentage of participants who passed the minimal clinically important differences of the FMA-UE will be compared using chi-square tests between the 3 groups.

The mean power across the assessment “time” (ie, T0 and T2) related to the action observation condition will be implemented in a mixed-design ANOVA to evaluate significant changes. A separate ANOVA will be performed to assess power changes in the stimuli selection data, using “treatment” (ie, EG@Hosp vs EG@Home vs CG) as the between-subjects factor and action as the within-subjects factor. To assess the predictive value of biomarkers for AOT effectiveness, an analysis of covariance (ANCOVA) will be performed considering the clinical data as the dependent variable, the “group” as a fixed factor, and the biomarkers as covariates.

Subsequently, to evaluate kinematic parameters recovery, a mixed design ANOVA will be implemented with “time” and “treatment” as within- and between-subjects factors, respectively.

The level of significance will be set at *P*<.05. For post hoc comparisons, the level of significance will be set at *P*<.017 after Bonferroni adjustment (.05/n; the number of comparisons, n=3) for the comparison of interaction effects. Cohen *d* will be calculated to determine the effect size of the change in scores for the behavioral motor outcomes between the groups. Immediate training effects (data from T0-T2) and the durability of training effects (data from T2-T3) will be separately investigated using mixed effect models.

Clinical-neurophysiological correlations will also be analyzed: the correlation between the ERD and factors such as the clinical scale score will be studied. To evaluate the differences in trends related to the clinical evolution of the patients, we will define a new variable to group the participants according to the presence or absence of relevant clinical improvements. The relevant clinical improvement will be defined by a clinical specialist for this purpose.

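### Baseline comparability of three arms is to be tested with two-group tests, which can over-report imbalance if the arms are compared pairwise at .05

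*Protocol article*

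**What the plan says.** The Methods overview allocates patients to the hospital AOT group, "experimental group at home (EG@Home), or control group (CG) in a 1:1:1 ratio". The Sample Size section gives the numbers: "we plan to recruit 20 participants for each group (a total of 60 participants) for this study".

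Under Baseline Comparability Analysis, "The baseline characteristics of the participants will be summarized and compared". For quantitative variables the section offers the 2-tailed t "test or nonparametric statistical method will be used for quantitative data". For the rest, "Categorical data will be analyzed using chi-square or Fisher exact tests and the Wilcoxon test".

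The Analysis of the Effectiveness section handles three arms differently. Group is a three-level factor in the ANOVA, the proportions passing the minimal clinically important difference are compared across all three groups by chi-square, and a threshold of .017 applies "after Bonferroni adjustment (.05/n; the number of comparisons, n=3) for the comparison of interaction effects". That threshold is not extended to the baseline tests.

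**The concern.** A t test cannot give one comparison of three arms. It has to be run pair by pair, and the section does not say which pairs or at what level. If each pair is tested at .05 and any significant pair is read as imbalance, the error rate per variable exceeds the nominal 5%.

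The Wilcoxon entry raises a similar problem. The rank-sum form compares two groups, the signed-rank form compares paired values, and neither has a meaning for unordered categories.

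Under valid randomisation, a significant baseline difference is in any case a chance finding, so these P values say little about comparability. What is at stake is the comparability statement in the report: with 20 per arm, a reader could take a chance difference as evidence of unbalanced groups.

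**Working it through.** **Inputs.** Three arms, 1:1:1 (Methods, Overview). 60 patients, 20 per arm; 54 required before a 10% dropout allowance (Sample Size). Significance level .05, and .05/3 for post hoc comparisons (Analysis of the Effectiveness).

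**1. The plan's own figures.** .05/3 = .0167, which rounds to the stated .017. 54/(1 − 0.10) = 60, and 60/3 = 20 per arm. Without the dropout allowance, 54/3 = 18 per arm. Both reproduce.

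**2. Number of pairs.** Three arms give 3 × 2/2 = 3 pairwise t tests per quantitative variable.

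**3. Reference value.** If the three tests were independent, the chance of at least one P < .05 with no true difference would be 1 − 0.95³ = 14.3%. The pairs share arms, so the true figure is lower.

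**4. Simulation.** 200,000 trials per arm size, normal data, no true difference, three equal arms:

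| Rule for flagging a variable | 20 per arm | 18 per arm |
|---|---|---|
| One given pair, t test at .05 | 4.9% to 5.0% | 5.0% to 5.1% |
| Any of three pairs, t test at .05 | 12.1% | 12.3% |
| Any of three pairs, t test at .05/3 | 4.3% | 4.4% |
| One-way ANOVA F test at .05 | 4.9% | 5.0% |

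As a cross-check, a studentized-range calculation with variance pooled over the three arms (57 degrees of freedom) and the two-group critical value (38 degrees of freedom) gives 11.6%, close to the simulated 12.1%.

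**5. Several variables.** The document does not fix the number of baseline variables. Assume 8 to 12, all independent. The chance of at least one flag is 1 − (1 − p)^k:

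- Three unadjusted pairwise t tests, p = 0.121: 1 − 0.879⁸ = 64%; 1 − 0.879¹² = 79%.
- One correct three-group test, p = 0.05: 1 − 0.95⁸ = 34%; 1 − 0.95¹² = 46%.

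The two-group test accounts only for the gap between the two lines, about 30 percentage points (64 − 34 = 30; 79 − 46 = 33). The rest comes from testing many variables. Several baseline variables would be scales of arm function or daily activity in the same patients, so they are correlated, which lowers both sets of figures.

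**6. Categorical data.** Chi-square and Fisher exact tests handle three groups in one test, so the inflation in step 4 does not arise for variables analysed that way. It could arise only for ordered categories compared pairwise by Wilcoxon.

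**The case against.** The baseline paragraph is a short list of test families in a condensed article, and the choice of omnibus test or of pairs is a detail that such an article can leave to the full protocol or analysis plan. The nonparametric method is unnamed and could be a three-group test such as Kruskal-Wallis. Each single pairwise t test keeps its 5% level. Elsewhere the plan treats group as three levels and recognises the cost of three comparisons. For categorical data, chi-square and Fisher exact come first and suit three arms, and Wilcoxon is reasonable for ordered measures; the article itself calls the Modified Barthel Index ordinal.

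Much of this stands. A reader might infer that the plan will flag 12% of null variables. The document does not support that: it does not say that all three pairs will be tested, each at .05, with any one counted as imbalance. Nor does it say that Wilcoxon will be used on unordered categories.

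The appeal to brevity does not remove the point. The t test is not an omitted detail. It is the one test named for quantitative data, and it does not fit three arms. The unnamed alternative does not mend it, and the only rank test named in the section is a two-group test. Wilcoxon can serve ordinal data, but across three arms only pair by pair.

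**Conclusion.** The point holds, as a minor one. The only test named for quantitative baseline data is a two-group test in a three-arm trial, without pairs or adjustment, and the baseline section does not match the plan's own three-level treatment of group in the effectiveness analysis.

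Its size is about 12% against about 5% per quantitative variable. This assumes normal data, no true difference, all three pairs tested unadjusted at .05, and any significant pair read as imbalance. The 64% to 79% chance of at least one flag should be cited only beside its 34% to 46% comparator, with the assumed 8 to 12 independent variables stated.

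Two stronger conclusions are tempting. One is that the tests would drive covariate selection or a claim that randomisation failed. The other is that the primary result is affected. The document supports neither: it ties no covariate choice, exclusion or other decision to a baseline P value, and the FMA-UE analysis is specified without reference to the baseline tests. The possible harm is a misleading comparability statement.

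**What to change.** Preferred: remove the baseline significance tests and report mean (SD), median (IQR) or counts by arm.

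If tests are kept, name one-way ANOVA or Kruskal-Wallis across the three arms for quantitative and ordinal variables, and chi-square or Fisher exact for nominal variables. Remove Wilcoxon from the sentence on categorical data.

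In either case, state in advance that the FMA-UE comparison is adjusted for its T0 value, whatever imbalance is observed, so that no baseline P value has a part in the choice. T0 is at present a level of the time factor, so the wording must say how it enters the adjusted model. This is a companion to the main change, and the point on the baseline tests stands without it.

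The cost is wording in the analysis section. No data, patients or procedures are affected.
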